### Randomisation

An individual not associated with the trial will perform the randomisation based on a computer- generated random number system. Group notification will be in a sealed envelope given to women after completion of the baseline measurement.

### The yoga intervention

The yoga intervention will consist of a weekly 90-minute yoga class for eight weeks by a qualified, accredited and experienced yoga teacher. Participants will also be given a 45-minute DVD made especially for this trial, with a shorter version of the class, and instructed to perform it daily. They will be given a log, in order to record their home sessions and make relevant comments.

Yoga practices and instruction approaches will be based on the Satyananda yoga® style of teaching. The breathing and *pranayama,* physical postures, meditation and relaxation techniques have systemised practices that will be taught to ensure uniformity of practice for outcomes [42]. This style, with its gentle repetitions of physical movements followed by rests, and use of modifications, may be well-suited to yoga for BCRL. Options for modifications will allow an individualised approach based on comfort, needs and preferences, in both the class and the home-practice DVD. Practices will be progressive during the eight weeks of the intervention.

The yoga intervention proposed in this study will consist of slow and deep breathing, a series of moving yoga postures followed by rests, *pranayama*, meditation based on mindfulness practices, and deep relaxation with arm elevation. The practices will be chosen to promote lymphatic clearing, improved postural awareness of the thoracic and shoulder area, as well as stress reduction.

Each yoga session will have appropriate warm-up and cool-down, following the guidelines of exercise for women with BCRL. The temperature of the room will be controlled to between 19–22 degrees Celsius (suitable for Tasmania) to ensure it does not become too hot, which can overload the lymphatic system [16].

### Primary and secondary outcomes

#### Characteristics of the sample

Women will complete questionnaires on demographic information, current health, as well as medical history pertaining to breast cancer and its treatment, and lymphoedema, onset and treatment prior to measurement. The completed questionnaires will be brought in at baseline, collected and entered into a specifically designed trial database.

### Primary outcome measures

#### Lymphoedema

All measurements of lymphoedema will be conducted with the participant resting in a supine position, with any compression sleeve removed. Due to the effect on the calculation of lymphoedema, the dominant and affected arm will be noted, and weight and height measured on the same equipment each time to calculate BMI.

#### Extra-cellular fluid

Extra-cellular fluid will be measured according to a recognized protocol [41], using bio-impedance L-dex™ XCA (Bio-Impedimed, Queensland), with electrodes placed at anatomical landmarks at the wrist of each arm and right ankle. An increase in extra-cellular fluid is paralleled by a decrease in impedance from the low-frequency electrical current. The result is recorded as a ratio to the non-affected limb, taking into account arm dominance [43]. As lymphoedema increases, so does the ratio of impedance [44]. The result, calculated from software provided by Bio-Impedimed, is recorded as an l-dex reading and any reading equal or higher than ten is considered an indication of clinically manifest lymphoedema.

#### Volume and percentage volume of arm and hand lymphoedema

Circumferential readings will be based on the protocol of the Australasian Lymphology Association [45], modified so the woman is lying not sitting. Both arms will be marked at the metacarpophalangeal joint, ulnar styloid and 10, 20, 30, 40 centimetres (cm) from the styloid process, using a pen and set square on the medial and lateral aspect of the arm, then circumference measured at each point by a Job non-stretch tape, recorded in cm. Finger circumferences will be measured distal to the web space, and recorded in millimetres (mm). Volume of lymphoedema and percentage of lymphoedema in the arm and hand will be calculated using the truncated cone formula [46] from the addition of circumference readings, using software provided by Flinders Lymphoedema Clinic, South Australia (SA), which compares the affected to the non-affected arm. An increase in fluid volume and % fluid volume readings equates to an increase in level of lymphoedema. Fluid volume will be recorded as millilitres (ml) and % fluid volume of ml.

#### Density of fibrous tissue

Density of fibrous tissue will be measured by a digital tonometer, model 1383 (Bio-medical Engineering, Flinders Medical Centre, SA), validated especially for this population [47,48], with an established protocol [49]. Tonometer measurements will be taken on the forearm 10 cm from the cubital fossa and on the upper arm 10 cm up from the cubital fossa in the middle of the lymph territory. Additional measurements will be taken at the anterior trunk at mid-clavicular line between the second and third ribs and the posterior trunk between the acromion and the first thoracic rib in the subscapular fossa. The digital tonometer measures the resistance of the tissues to compression - that is, the amount of fibrotic induration (collagen build-up) in the superficial tissues at a given point [46,50]. Each measurement will be followed by a three-second pause before retesting. A higher score for the digital tonometer denotes a higher level of tissue density. The result will be recorded in mm and the average of three recorded.

#### Physical sensations associated with lymphoedema

Visual Analogue Scales (VAS) have been validated as an effective method of recording individual perceptions of subjective parameters such as pain [51], and adapted in lymphoedema trials to include sensations specific to lymphoedema [40,52].

A VAS scale that has been developed for this trial will be used to measure the severity of lymphoedema sensations which each woman will define, such as heaviness, tingling, aching. The VAS scale will also measure pain and fatigue, and the degree to which sensations, pain and fatigue have limited her activity for that day. The VAS scale will record what each woman felt on the day of measurement. The scale is scored as 0 cm being ‘no discomfort’ and 10 cm being ‘the worst imaginable’.

#### Quality of life

A validated questionnaire [15], developed specifically to measure quality of life for people with lymphoedema (LYMQOL), will be used. Its upper limb version will be used in this trial. Scores are recorded for the day of measurement. Total quality of life score is recorded between 0–10, ten being the best and zero the worst. Its result is recorded as the number the woman recorded from 1 to 10. Independent scales for function, symptoms, appearance, emotions, are also included in the questionnaire. Each of these includes several questions which are marked from 1 to 4, four being the worst. The sum of answers for each area of function, symptoms, appearance and emotions are added, then divided by the number of questions in that section to give a score for each parameter. A higher score denotes a lower quality of life associated with that parameter. In this way, different aspects of quality of life can be recorded numerically and compared between intervention and control groups.

### Secondary outcomes measures

#### Range of motion of shoulder

The range of motion (ROM) of the shoulder of the non-affected, followed by the affected, arm will be measured using a two-armed goniometer, which has been validated for clinical trials [53] and used in trials for women with BCRL [54,55]. An established protocol [56] will be followed . Women will sit in a low-back chair with stable shoulder blades, and suitable back support, their knees bent to 90° and with their feet at hip width and flat on the floor. *Flexion**abduction* and *extension* of the shoulder in the sagittal or coronal planes will be measured from the starting point of arms in anatomical position. *Interna*l and *external rotation* of the shoulder will be measured from the starting position of the arm abducted to 90°, forearm pronated and parallel to floor, palm down, with elbow bent to 90°. To prevent fatigue, the testing will be conducted in the following order: *flexi*o*n**internal rotation**extension**abduction**external rotation*. Endpoint of measurement will be full range, compensatory movements of the shoulder or trunk occurring, or women experiencing pain or tightness. The final result will be recorded in degrees as the best of three attempts. The higher the score the greater the range of motion.

#### Strength of shoulder

Muscle strength will be assessed using a Commander Powertrack II Muscle Tester (JTechMedical, Salt Lake City, Utah, USA), validated in a healthy population [57] and used in lymphoedema trials [7,58] following an established protocol for muscle testing [59]. The participant will sit in a stable position and the non-affected, then the affected, arm measured in turn, three times for each test. The arm will be raised to 90° for measurement of strength for *flexion**horizontal adduction* and *abduction.* The arm will be positioned slightly across the body for measurement of strength for *pectoralis major* and the arm elevated to 120° for strength of *serratus anterior*. To measure the strength of *extension,* the participant’s arm will be by her side. *Pectoralis minor* strength will be assessed with the participant in supine position. This is also the order of testing to prevent fatigue.

The strength of the arm or shoulder will be measured from the force applied against the resisted hand-held dynamometer, held by the assessor for a count of three seconds. Measurement will cease when full strength is applied, compensatory movements of the shoulder or trunk occur or pain is experienced. The best of three attempts will be recorded in Newtons (n). A high score denotes a stronger muscle action.

#### Grip strength

Hand grip strength will be assessed by using a hand-held grip dynamometer (Smedleys, TTM, http://www.stoeltingco.com), which has been validated for use in a clinical setting [60], and using a protocol common to lymphoedema trials [58]. The participant will sit in a stable position with her elbow bent at 90° and close to their body, palm facing inwards. Grip strength will be assessed by applying pressure to the dynamometer with the non-affected, followed by the affected, hand. Measurement ceases at full strength or if pain or instability occurs. The best of three attempts will be recorded in kilograms (kg). A high score denotes stronger grip strength.

#### Thoracic spine mobility

Thoracic spine mobility will be measured dynamically using video analysis in order to quantify the functional mobility of the spine during *flexion/extension, lateral flexion* and *rotation* following a validated protocol. [61]. Range of motion will be recorded by a video camera with backlighting, utilising reflective surface markers. Reflective markers will be placed on women’s skin at the following locations: left and right superior posterior iliac spines (LPSI, RPSI), spinal processes (S1, L3, L1, T6, T1) and left and right acromion (LACR, RACR). Reflective markers will also be placed on the wall behind, or on the floor around the chair in the case of rotation, to provide calibration references. At the initial assessment, the placement of markers will be measured and recorded on the participant’s data sheet, to ensure consistency in the placement of markers at each measurement.

Women will be tested standing in stable anatomical position for *flexion/extension* and *lateral flexion* with the camera at a distance of two metres, and in stable sitting position for *rotation* with the camera one metre overhead. The test will be performed three times with each movement stopping at the point of full range, instability or pain.

Video footage will be downloaded at the end of each measurement. Video data will then be analysed using Quintic™ sports biomechanics video analysis software 9.03 version 14 (http://www.quintic.com). Measures will be calculated from resting position to range in each direction and full range, and will be recorded in degrees from software specifically made for this trial (Human Life Sciences, UTAS), following the calculated measures described in another trial [61]. A higher score denotes greater movement. After analysis by Quintic, data will be entered into a specifically designed trial database.

As the use of video analysis with surface markers applied to the skin may be invasive for women who have been treated for breast cancer, women will have a choice of participation in this test.

#### Physical activity

Physical activity will be recorded at each session as it may impact other outcomes such as lymphoedema, sensation, pain, fatigue and arm movement. Physical activity in the week prior to each measurement period will be reported using the International Physical Activity Questionnaire (IPAQ-2005) short form, proven reliable in the Physical Activity for Lymphoedema (PAL) trial [62]. The questionnaire measures the amount of vigorous, moderate and walking activity in intensity and duration, as well as the number of minutes in sitting. The total time in each activity is multiplied by an intensity value to calculate total weekly activity reported in MET.min^-1^. The total MET.min^-1^ score will also be given a value of 1 = light; 2 = moderate; 3 = high. Sitting time is recorded as a total number of minutes for that week.

Physical activity for that day will be recorded on the VAS scale as a number from 0-10 with 0 indicating no activity and 10 indicating constant activity.

### Interview for yoga intervention women

A 20-minute audio-taped interview will be held at week 8 for the yoga intervention group and will be carried out by an independent assessor. Questions will be open-ended, in relation to the yoga sessions and DVD. Recorded interviews will be transcribed in full. An iterative-thematic approach will be used to analyse data by two researchers independently, then results compared and further analysis completed, by reporting data in themes and sub-themes according to frequency.

### Study measures at baseline and weeks 4, 8 and 12

All staff involved in measurements will be trained prior to commencement of baseline testing and use standardised protocol and validated instruments. Two qualified lymphoedema therapists will take the lymphoedema measurements, one in Hobart, one in Launceston. Other staff will be the same at both locations. All assessors will be blinded to group allocation and to previous results. Each measurement will be performed by the same assessor at each time-point.

Participants will be advised to abstain from alcohol 12 hours prior to testing, caffeine and heavy exercise two hours before and be allocated a time that will not change during the trial to ensure consistency of readings for lymphoedema levels.

Measurements for the thoracic spine sub-group will be held the day after the other measurements at baseline, weeks 8 and 12.

All equipment will be calibrated prior to each measurement period.

All data will be recorded onto a case record form for each woman then transcribed into a specifically designed trial database.

The study flow is summarized in Figure 1 and the study measurements in Table 1.

**Figure 1 F1:**
[figure not shown]
Flow chart of trial.

**Table 1 T1:** Outcome measurements at baseline, weeks 4, 8, 12

**Baseline week 0**	**Week 4**	**Week 8**	**Week 12**
**measurements**	**Measurements-after 4 weeks intervention**	**Measurements-at completion intervention**	**Follow-up measurements**
Collection of medical, demographic questionnaires		Intervention group: interviews	
Log of daily yoga practice to yoga group	Collection of daily yoga log	Collection of daily yoga log	
Lymph measures:	Lymph measures:	Lymph measures:	Lymph measures:
· Bio-impedance	· Bio-impedance	· Bio-impedance	· Bio-impedance
· Circumference	· Circumference	· Circumference	· Circumference
· Tonometer	· Tonometer	· Tonometer	· Tonometer
· VAS symptoms	· VAS symptoms	· VAS symptoms	· VAS symptoms
Weight/height BMI	Weight/BMI	Weight/BMI	Weight/BMI
Arm measures:	Arm measures:	Arm measures:	Arm measures:
· Arm strength	· Arm strength	· Arm strength	· Arm strength
· Shoulder ROM	· Shoulder ROM	· Shoulder ROM	· Shoulder ROM
QOL:	QOL:	QOL:	QOL:
LYMQOL questionnaire	LYMQOL questionnaire	LYMQOL questionnaire	LYMQOL questionnaire
Physical activity:	Physical activity:	Physical activity:	Physical activity:
· IPAQ –short form	· IPAQ –short form	· IPAQ –short form	· IPAQ –short form
· VAS day’s activity	· VAS day’s activity	· VAS day’s activity	· VAS day’s activity
Thoracic spine – sub group:		Thoracic spine – sub group:	Thoracic spine – sub group:
· Spinal ROM video		· Spinal ROM video	· Spinal ROM video

### Measurements at weeks 4, 8, 12

Measurements and sequence of measurements will be identical to baseline.

### Compliance for attendance at yoga and home-practice DVD

A protocol will be put in place should a woman in the intervention have to miss a class, so that another class may be organised when possible. Attendance at the yoga class will be recorded weekly and DVD compliance self-recorded in a log, collected at weeks 4 and 8.

### Data analysis

Medical and demographic information will be analysed using descriptive analysis within SPSS (version 19SPSS Inc. IBM, USA 2010) to calculate means and standard deviations or percentage values. Differences between groups will be assessed using t-tests for comparing continuous variables and chi-square tests for categorical variables.

All statistical analyses for quantitative measurements will be performed using STATA statistical software (version 12; 1985-2011; STATA corp.; College Station; Texas, USA). Binary categorical data will be analysed for variability between the groups using logistic regression. Parametric longitudinal data will be analysed via mixed methods linear regression. Non-parametric data will use ordinal logistic regression. Post-hoc testing will be performed on both parametric and non-parametric data using the Holms test to locate the means that are significantly different. Statistical significance will be set at p < 0.05.

Qualitative data from interviews will be analysed using an iterative-thematic approach.

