**Methods and design:**

A randomised controlled pilot trial will be conducted in Hobart and Launceston with a total of 40 women receiving either yoga intervention or current best practice care. Intervention will consist of eight weeks of a weekly teacher-led yoga class with a home-based daily yoga practice delivered by DVD. Primary outcome measures will be the effects of yoga on lymphoedema and its associated symptoms and quality of life. Secondary outcome measures will be range of motion of the arm and thoracic spine, shoulder strength, and weekly and daily physical activity. Primary and secondary outcomes will be measured at baseline, weeks four, eight and a four week follow up at week twelve. Range of motion of the spine, in a self-nominated group, will be measured at baseline, weeks eight and twelve. A further outcome will be the women’s perceptions of the yoga collected by interview at week eight.

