### Sample size calculation

An *a priori* sample size calculation based on clinically significant changes between groups of between 10-20% in primary outcome measures with standard deviations of between 12 and 15% of the mean, or within groups 10% difference with an SD of 20%, indicated that numbers of between 13 and 19 participants would be required per group. Consequently, we plan on recruiting 20 participants per group to allow for a small number of withdrawals.

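### Baseline characteristics are to be significance-tested, while the outcome models state no use of each outcome's pre-randomisation value

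*Protocol article*

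**What the plan says.** The first paragraph of Data analysis in the protocol article concerns the sample's characteristics: "Medical and demographic information will be analysed using descriptive analysis within SPSS". It continues: "Differences between groups will be assessed using t-tests for comparing continuous variables and chi-square tests for categorical variables". Read in place, these are between-arm tests of characteristics collected at baseline.

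The second paragraph turns to the outcomes. For continuous outcomes: "Parametric longitudinal data will be analysed via mixed methods linear regression". For the rest: "Non-parametric data will use ordinal logistic regression", with logistic regression for binary data. A Holm procedure is to locate which means differ, and "Statistical significance will be set at p < 0.05". No fixed effects, covariates or target contrast are named.

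Baseline values will exist. The abstract says: "Primary and secondary outcomes will be measured at baseline, weeks four, eight and a four week follow up at week twelve". Table 1 lists every quantitative outcome at week 0, and the Randomisation section has the allocation envelope handed over after baseline measurement. Thoracic spine mobility, in a self-chosen subgroup, is measured at weeks 0, 8 and 12 only.

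**The concern.** There are two linked problems.

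- **The tests.** Allocation is by computer-generated random numbers, so the null hypothesis of a baseline t-test or chi-square test is true by design. In a small trial a non-significant result gives false reassurance, and a significant one raises an alarm about a chance event.
- **The models.** The useful way to deal with chance imbalance is to condition on the baseline value of the outcome, and the article gives that value no stated role. A mixed regression on longitudinal data can be set up in several ways, and these differ in how they treat imbalance and in precision.

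At stake are the effect estimates and their standard errors for each quantitative outcome. With 40 women, a moderate chance imbalance is not rare.

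**Working it through.** **Inputs.** There are 20 women per arm (Sample size calculation). Alpha is 0.05 (Data analysis), taken as two-sided because sidedness is not stated. The correlation rho between baseline and follow-up is not in the documents, so 0.5, 0.7 and 0.9 are assumed. The formulas also assume equal variance at baseline and follow-up. The plan gives no figure of its own on this point to reproduce.

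**1. What the baseline t-test can show**

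- SE of a difference in baseline means, in SD units: sqrt(2/20) = 0.316.
- Largest non-significant gap: t(38, 0.975) × 0.316 = 2.024 × 0.316 = 0.64 SD.
- An observed gap of 0.5 SD gives t = 0.5/0.316 = 1.58, below 2.024, so it is called non-significant.
- Chance of a gap above 0.5 SD in either direction (normal approximation): 2 × [1 − Φ(1.58)] = 11%.
- With 10 to 20 independent tests (number assumed), the chance of at least one p < 0.05 is 1 − 0.95^10 = 40% to 1 − 0.95^20 = 64%.

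**2. How each use of baseline treats an imbalance**

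Let D be the observed baseline gap in SD units. The expected error in the estimated effect is rho × D if baseline is ignored, −(1 − rho) × D for the raw-change contrast, and 0 with baseline as a covariate. For D = 0.5:

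| rho | Baseline ignored | Raw change | Baseline covariate |
|---|---|---|---|
| 0.5 | +0.25 SD | −0.25 SD | 0 |
| 0.7 | +0.35 SD | −0.15 SD | 0 |
| 0.9 | +0.45 SD | −0.05 SD | 0 |

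If baseline is simply the first of four visits and the arms are compared through group-by-visit terms, the contrast at a later visit is the raw-change column.

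**3. Precision**

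Relative to a follow-up-only comparison, the variance factor is 2(1 − rho) for raw change and 1 − rho² for the covariate analysis. Their ratio is (1 − rho²)/[2(1 − rho)] = (1 + rho)/2.

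| rho | (1 + rho)/2 | Equivalent extra women, 1/ratio − 1 |
|---|---|---|
| 0.5 | 0.75 | 33% |
| 0.7 | 0.85 | 18% |
| 0.9 | 0.95 | 5% |

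**4. Check by simulation**

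Four-visit mixed models were simulated with compound symmetry, 20 per arm, SD 15 and 1,500 replicates. The SE of the week-8 effect was:

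| rho | Baseline ignored | Raw change | Baseline covariate | Baseline means constrained equal |
|---|---|---|---|---|
| 0.5 | 4.60 | 4.57 | 4.00 | 3.93 |
| 0.7 | 4.64 | 3.54 | 3.31 | 3.25 |
| 0.9 | 4.68 | 2.04 | 2.02 | 1.99 |

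The squared SE ratios, covariate to raw change, are (4.00/4.57)² = 0.77, (3.31/3.54)² = 0.87 and (2.02/2.04)² = 0.98. They lie slightly above the formula, as expected when a slope must be estimated from 40 women. At rho 0.7 the correlation of the estimate with the baseline imbalance was +0.71 with baseline ignored, −0.40 for raw change, 0.02 for the covariate analysis and 0.00 for the constrained one.

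**The case against.** The strongest reply is that the article is silent rather than wrong on adjustment. It names model families only, and covariates are commonly fixed in a full protocol or analysis plan, neither of which is shown. That stands as a limit on the claim. A reader might infer that the outcome models contain no baseline adjustment; the text neither includes nor excludes it. What remains is that the one between-group procedure stated for baseline data is uninformative, while the one that would help is not stated.

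Other stronger readings also go beyond the text:

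- **That imbalance is left uncorrected.** This is true if baseline is ignored. A group-by-visit contrast with baseline as a visit does subtract the gap, but by too much.
- **That the tests decide what is adjusted for.** No rule links their results to the models or to interpretation. As written they change no estimate, and taken alone they are a reporting matter.
- **That averaging the baseline visit into one group effect dilutes it.** The article specifies no such single group term over all four visits.
- **That the trial is short of power and so cannot spare the precision.** The sample size section states no power. It works from "clinically significant changes between groups of between 10-20% in primary outcome measures with standard deviations of between 12 and 15% of the mean", which does not settle whether the SD is that of a measurement or of a change. Any shortfall also depends on an unknown correlation.

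It is also fair that the precision gain is uncertain. At rho 0.9 it is close to nil against raw change. The gain in handling imbalance is then small against raw change too, but remains large against an analysis that ignores baseline.

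**Conclusion.** The point holds in a limited form. The planned significance tests of baseline characteristics are uninformative in a randomised trial, and at 20 per arm they would pass observed gaps of up to 0.64 SD. The named outcome models state no use of the pre-randomisation value of each outcome. Conditioning on that value is better than either obvious alternative. Against raw change it multiplies the variance by 0.75 to 0.95 for rho from 0.5 to 0.9 (0.77 to 0.98 in simulation at this sample size) and avoids over-correction. Against ignoring baseline it removes the expected carry-over of rho × D.

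These sizes rest on an assumed correlation, equal variances over time and approximately linear, continuous outcomes. The variance ratio does not carry over directly to the ordinal and binary models. The conclusion is an improvement worth making to the analysis wording; it does not show that the planned analysis is invalid.

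**What to change.** In Data analysis:

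1. Remove the t-tests and chi-square tests on medical and demographic data. Present these by arm with the means, standard deviations and percentages already planned.
2. State that each quantitative outcome will be analysed at its scheduled post-baseline visits (weeks 4, 8 and 12; weeks 8 and 12 for thoracic spine mobility) with group, visit, group-by-visit and the woman's baseline value of that outcome as a covariate. Alternatively, keep baseline in the outcome vector with arm means constrained equal at week 0. Choose one form in advance, and include the baseline value in the ordinal and logistic models too.
3. State that this applies whatever imbalance is observed.
4. Report the adjusted between-group difference with its 95% confidence interval.

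If a full protocol or analysis plan already says this, a cross-reference is enough. The cost is a few sentences and one extra model parameter per outcome. No new data, visits or participants are needed.

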## Methods/design

### Study design and setting

This study is designed to be a randomised controlled trial for women with stage one BCRL, as defined by the International Society of Lymphology [16]. The study will compare the results of a group who receive an integrated yoga intervention, to a control group who will continue to follow current best-practice in self-management of lymphoedema from a manual given to all participants pre-randomisation, but who will receive no yoga intervention. The control group will be wait-listed for the yoga intervention and so will be invited to participate at the completion of the study.

Measurements will be conducted at baseline (week 0), after which participants will be randomised to the yoga intervention or the control group. Further measurements will be made at week 4 (mid-point), week 8 (on completion of the yoga) and at week 12 (four weeks after the intervention).

The trial will be held at two locations, Hobart and Launceston. Both locations will consist of an intervention and control group. The study will be conducted at Community Health Centres in both locations.

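### Yoga is delivered in shared classes in one arm only, but the 20 per group is set as if all women were independent; at an assumed class ICC of 0.05 it is worth about 16 per group

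*Protocol article*

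**What the plan says.** All places are in the protocol article.

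- **The yoga intervention:** "The yoga intervention will consist of a weekly 90-minute yoga class for eight weeks by a qualified, accredited and experienced yoga teacher". Women also get a 45-minute DVD to use daily at home.
- **Study design and setting:** "Both locations will consist of an intervention and control group". Controls follow a self-management manual and have no yoga until the study ends. The number and size of classes at each location are not stated.
- **Randomisation:** women are allocated individually, by sealed envelope after the baseline measurement.
- **Sample size calculation:** the inputs are "clinically significant changes between groups of between 10-20% in primary outcome measures" with "standard deviations of between 12 and 15% of the mean", or alternatively "within groups 10% difference with an SD of 20" per cent. These "indicated that numbers of between 13 and 19 participants would be required per group". Twenty per group are to be recruited, and the only reason given for the margin is a few withdrawals.
- **Data analysis:** "Parametric longitudinal data will be analysed via mixed methods linear regression", with logistic and ordinal logistic regression for other outcomes, and "Statistical significance will be set at p < 0.05". No class, teacher or location term is named. The random effects of the mixed model are not specified.

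**The concern.** This is a partially clustered design. Women in the same yoga class share sessions, fellow participants and teacher for eight weeks, so their outcomes can become correlated after randomisation. Controls share nothing comparable. Balancing allocation by location would not remove this, and nor would a location term common to both arms, because the correlation arises in one arm only.

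A sample size built from a difference and an SD assumes independent women. If class correlation is positive, 20 per group delivers less than stated, and an analysis without allowance for class gives intervals that are too narrow and p-values that are too small. The trial tests at the 5% level, and its Discussion says that its methods should inform larger studies, so the omission could be carried forward.

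**Working it through.** **Inputs from the protocol article:** 20 per group; difference 10% to 20%; SD 12% to 15%; significance level 0.05 (taken as two-sided); stated requirement 13 to 19 per group.

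**Assumptions, not in the document:** two yoga classes of 10, one per location; ICC 0.05, with range 0.01 to 0.10; one time point.

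**1. The plan's own figure.** The two-sample formula is n = 2 × (1.96 + 0.84)² × (SD/difference)², at 80% power (power is not stated).
- 10% difference: SD 12% gives 23 per group and SD 15% gives 36.
- 20% difference: 6 and 9.
- Within-group case (10%, SD 20%): 32, or 34 with the t distribution.

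The range 13 to 19 is therefore not reproduced as a two-group requirement. A one-sample or paired t formula with a 10% difference and SD 12% to 15% comes close (13.3 to 19.7). That is a separate and larger problem. Here 13 to 19 serves only as the plan's own benchmark. None of these formulas contains a clustering term.

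**2. Loss of precision.** The yoga-arm design effect is DE = 1 + (10 − 1) × ICC. Controls are not in classes, so the variance of the difference grows by (DE + 1)/2 and the standard error by its square root. The equivalent number of independent women per arm is 20 ÷ [(DE + 1)/2].

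| ICC | DE | Variance ratio | SE factor | Two-arm equivalent n per arm |
|---|---|---|---|---|
| 0.01 | 1.09 | 1.045 | 1.02 | 19.1 |
| 0.05 | 1.45 | 1.225 | 1.11 | 16.3 |
| 0.10 | 1.90 | 1.450 | 1.20 | 13.8 |

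**3. When does 20 stop covering 19?** Set 20 ÷ [(DE + 1)/2] = 19. Then (DE + 1)/2 = 1.0526, DE = 1.105 and ICC = 0.105/9 ≈ 0.012, before any withdrawal. With two withdrawals per arm (18 women, classes of 9) at ICC 0.05, DE = 1.40 and the equivalent is 18/1.20 = 15.0 per arm.

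**4. Smaller classes.** With four classes of 5 at ICC 0.05, DE = 1.20, the variance ratio is 1.10, the SE factor is 1.05 and the equivalent is 20/1.10 = 18.2 per arm.

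**5. False-positive rate if class is ignored.** Simulation of an ordinary t-test, 20 v 20 with two yoga classes of 10 (40,000 replicates), gives 5.5%, 7.5% and 10.3% at ICC 0.01, 0.05 and 0.10. The normal approximation, 2 × [1 − Φ(1.96/SE factor)], gives 5.5%, 7.7% and 10.4%.

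**6. Power with the correct variance.** Power = Φ(difference/SE − 1.96), with SE = SD × √(2/20) × SE factor.

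| Difference, SD | ICC 0 | ICC 0.01 | ICC 0.05 | ICC 0.10 |
|---|---|---|---|---|
| 10%, 12% | 75.0% | 73.2% | 66.3% | 59.0% |
| 10%, 15% | 55.9% | 54.1% | 47.8% | 41.7% |
| 20%, 15% | 98.8% | 98.5% | 96.8% | 93.8% |

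**The case against.** **The analysis section does not say that women are treated as independent.** A reader might infer it. The section names a mixed model without its random effects, and an article may leave that detail to the full protocol or analysis plan. This stands. What can be said is that no allowance for class is described. The firm anchor is the sample size section, which fixes the number and names withdrawals as its only allowance.

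**The size is assumed.** Neither the ICC nor the number of classes is in the document, and make-up classes for missed sessions may blur class membership. Content is standardised. The daily DVD comes to 7 × 45 = 315 minutes a week against 90 in class, so only 90/405, about 22%, of prescribed practice is shared. The ICC could be near 0.01, where the standard error moves by 2%. This stands, and is why only a range is given.

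**A reader might infer that 20 yoga women count as about 14, or fewer than 13 after two withdrawals (18/1.40 = 12.9), and so fall below the plan's lower figure.** That sets a one-arm figure against a requirement for two equal arms. Controls lose nothing, so the comparable figures are 16.3 and 15.0, both inside 13 to 19.

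**The non-reproducible 13 to 19 matters more.** True: power for a 10% difference is only 56% to 75% before clustering. That does not remove the clustering loss, which comes on top.

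**Conclusion.** The point holds in a limited form. Group delivery in one arm is explicit, and the stated sample size makes no allowance for it. If class correlation is positive, 20 per group buys less than stated and any analysis that ignores class is too optimistic. With two classes of 10, the upper requirement of 19 is no longer covered once the ICC exceeds about 0.012; at 0.05 the equivalent is about 16 per arm, and the standard error should be 11% larger. The power loss is 8 to 9 percentage points for a 10% difference and 2 points for 20% with SD 15%.

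These sizes rest on an assumed ICC and an inferred class number; more and smaller classes would lose less. The document does not show that the models assume independence, or that the trial falls below its own lower requirement of 13.

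**What to change.** **Sample size calculation.** State that yoga is given in classes, give the expected number and size of classes, and report what 20 per group delivers over an assumed ICC range as a two-arm equivalent (about 19, 16 and 14 per arm at ICC 0.01, 0.05 and 0.10 for two classes of 10). Remove the implication that 20 covers 13 to 19 with room for withdrawals.

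**Data analysis.** For each primary outcome add a sensitivity analysis that reports the yoga-control difference by location (class) and an interval with the standard error multiplied by 1.02, 1.11 and 1.20, recalculated for the classes actually run. Describe the main interval as conditional on those classes.

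Do not make a fixed ICC of 0.05 a decision rule, since the value is assumed. Do not rely on a class random effect either: about two classes leave roughly one degree of freedom for that variance.

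**Cost.** Wording in two sections and a small analysis of data already collected. The sensitivity intervals are 2% to 20% wider and the sample size statement is less favourable.
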